## Abstract

**Background:**

Dental anxiety and anxiety-related avoidance of dental care create significant problems for patients and the dental profession. Distraction interventions are used in daily medical practice to help patients cope with unpleasant procedures. There is evidence that exposure to natural scenery is beneficial for patients and that the use of virtual reality (VR) distraction is more effective than other distraction interventions, such as watching television. The main aim of this randomized controlled trial is to determine whether the use of VR during dental treatment can improve the overall dental experience and recollections of treatment for patients, breaking the negative cycle of memories of anxiety leading to further anxiety, and avoidance of future dental appointments. Additionally, the aim is to test whether VR benefits dental patients with all levels of dental anxiety or whether it could be especially beneficial for patients suffering from higher levels of dental anxiety. The third aim is to test whether the content of the VR distraction can make a difference for its effectiveness by comparing two types of virtual environments, a natural environment and an urban environment.

**Methods/design:**

The effectiveness of VR distraction will be examined in patients 18 years or older who are scheduled to undergo dental treatment for fillings and/or extractions, with a maximum length of 30 minutes. Patients will be randomly allocated into one of three groups. The first group will be exposed to a VR of a natural environment. The second group will be exposed to a VR of an urban environment. A third group consists of patients who receive standard care (control group). Primary outcomes relate to patients’ memories of the dental treatment one week after treatment: (a) remembered pain, (b) intrusive thoughts and (c) vividness of memories. Other measures of interest are the dental experience, the treatment experience and the VR experience.

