#### *Overall hypotheses:*

1. Virtual reality exposure will lead to less intrusive thoughts, less vivid memories, less remembered pain and better overall dental experiences.

2. Dental anxiety will moderate the proposed effects under hypothesis 1. Patients with more dental anxiety will benefit more from the use of VR than patients with less dental anxiety.

3. The natural VR environment will be more effective than the urban VR environment.

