### Sample size

Given the novel approach of this study, there is little comparable research available to use for a sample size calculation. We are also somewhat restricted by the number of potential patients available within a given time period in the dental practice. However, we do have data from our own pilot work in a simulated dental setting, which we have used to make an informed estimate of the required sample size for the current study.

The sample size calculation (with a power of 0.80, significance level of 0.05 and based on 2-sided testing) is based on one of the main outcomes related to memories, ‘intrusive thoughts’, as measured with an 11-point verbal rating scale. In our pilot study, the standard deviation for this outcome in our control group was 1.25 and we have conservatively used an estimated standard deviation of 1.3 in this sample size calculation. Based on these assumptions, and comparing the two VR groups against the control group, following up a total sample size of 90 patients (that is, 30 per group) would allow the detection of a between-group difference of around 0.82 units (that is, a moderate effect size). Since drop-outs are unavoidable when collecting follow-up data, this number needs to be adjusted for the estimated drop-out rate. In our simulation study, we had a drop-out rate of 10% for collecting the follow-up data, but since we paid participants for participation in that study (although they received their pay after the simulated treatment and before participating in the follow-up interview), we anticipate a higher drop-out rate for this study, and have allowed for a 15% drop-out rate. Adjusting the sample size for this drop-out rate results in a sample of 108 patients needing to be recruited.

The use of technical computer equipment is associated with the risk of technical failures. In the pilot study we had to exclude 6 of 75 participants because the VR crashed or the remote stopped working during the simulated treatment and the participant was no longer able to interact with the VR environment. Several improvements in the VR program have been made since, such as putting force fields in place that restrict the area of virtual exploration, but we still anticipate the exclusion of participants because of technical issues. We will therefore increase the sample size by a further 8%, resulting in a total recruitment target of 120 for this study (that is, 40 patients per group).

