### Data analysis

The data will be recorded and analyzed using SPSS 20.0. All data will be analyzed using an intention-to-treat analysis. Descriptive statistics will be calculated. Discrete variables will be summarized by frequencies or proportions. Continuous variables will be reported as means and standard errors or medians and range (depending on the distribution of the variables). Data will be checked for baseline differences between the treatment arms. If baseline differences do occur for any of the variables, they will be added to subsequent models to compensate for those differences using an analysis of covariance approach.

Analyses of covariance (ANCOVAs) will be performed for each of the outcome measures with VR condition (that is, natural, urban or control) as the independent variable and baseline dental anxiety as the covariate, including planned contrasts to explore specific hypotheses. Contrasts for VR condition will be based on comparisons of VR (both natural and urban environments combined) with the no VR control group (comparison 1), natural VR with urban VR (comparison 2), natural VR with the control group and urban VR with the control group (Table 2 gives an overview of specific predictions being tested).

**Table 2 T2:** Overview of the specific comparisons for each prediction

	**Prediction**	**Comparison 1:**	**Comparison 2:**	**Comparison 3:**
		**virtual reality (both natural and urban environments) vs no virtual reality (control group)**	**natural virtual reality vs urban virtual reality**	**(a) natural virtual reality vs control**

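### Three unranked primary outcomes share hypothesis 1, but the whole two-sided 0.05 is spent on one of them, so the chance of a false positive on hypothesis 1 is about 8–14%

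*Protocol article*

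**What the plan says.** - **Primary outcomes.** The Abstract (Methods/design) lists three outcomes at one week: "a) remembered pain, (b) intrusive thoughts and (c) vividness of memories". Main study parameters lists the same three with some further memory items, again unranked.
- **Hypotheses.** Overall hypothesis 1 reads: "Virtual reality exposure will lead to less intrusive thoughts, less vivid memories, less remembered pain and better overall dental experiences". Hypothesis 2 is moderation by dental anxiety. Hypothesis 3 is that natural VR outperforms urban VR.
- **Sample size.** The calculation "is based on one of the main outcomes related to memories", namely intrusive thoughts. It is made "with a power of 0.80, significance level of 0.05 and based on 2-sided testing", for the contrast "comparing the two VR groups against the control group".
- **Analysis.** Data analysis plans one ANCOVA per outcome with planned contrasts: comparison 1 (pooled VR against control), comparison 2 (natural against urban), and then "natural VR with the control group and urban VR with the control group", which Table 2 calls comparisons 3a and 3b.
- **Table 2.** Hypotheses 1 and 2 are tied to comparison 1. Hypothesis 3 is tied to comparisons 2, 3a and 3b.

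The 0.05 level appears only under Sample size. The article does not order the tests, make one conditional on another, or say how many primary outcomes must succeed for hypothesis 1.

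**The concern.** A trial with three primary outcomes needs a rule for turning three results into one conclusion. Without one, a significant result on any of the three could be reported as support for hypothesis 1, and the 0.05 used for sizing would no longer describe the risk of a false claim. The sample size leaves little room for a later correction, because it spends all of 0.05 on one outcome and one contrast.

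A smaller problem lies in the hypothesis 3 row of Table 2. Comparisons 3a and 3b set each VR group against control. If one is significant and the other is not, that does not show that natural VR beats urban VR. Only comparison 2 tests that.

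**Working it through.** **1. Reproduce the stated sample size.** Inputs from Sample size: the plan "conservatively used an estimated standard deviation of 1.3", a difference of about 0.82, power 0.80, two-sided 0.05, and "following up a total sample size of 90 patients (that is, 30 per group").

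- Standard error of pooled VR (60) against control (30): 1.3 × √(1/60 + 1/30) = 0.2907.
- Detectable difference: (1.960 + 0.842) × 0.2907 = 0.814 (0.823 with the t distribution). The protocol says about 0.82.
- Power at 0.82: Φ(0.82/0.2907 − 1.960) = Φ(0.861) = 0.805 (t-based 0.797).
- Inflation per group: 30/0.85 → 36 (108 in all), then 36/0.92 → 40 (120 in all).
- Check on the contrast: 30 against 30 would give a detectable difference of 2.802 × 1.3 × √(2/30) = 0.94 and power 0.685 at 0.82, which does not fit.

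The arithmetic is therefore correct, and it spends the full 0.05 on one outcome and comparison 1.

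**2. False-positive risk for hypothesis 1.** Three outcomes are tested on comparison 1, each at 0.05, and any one counts. For independent outcomes the formula gives 1 − 0.95³ = 0.143. For correlated outcomes a simulation was run under no effect of VR on any outcome: 200,000 trials, 30 per group, normal data, equal correlation between outcomes, pooled-variance t tests on 87 df, anxiety covariate left out. The article gives no correlation, so a range is shown. The last column is a secondary figure.

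| Assumed correlation | Comparison 1, three outcomes | Multiple of 0.05 | All four contrasts, three outcomes |
|---|---|---|---|
| 0 | 0.142 | 2.8 | 0.334 |
| 0.5 | 0.125 | 2.5 | 0.295 |
| 0.7 | 0.109 | 2.2 | 0.258 |
| 0.9 | 0.083 | 1.7 | 0.203 |

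**3. Cost of a Bonferroni correction at the planned size.** The level becomes 0.05/3 = 0.0167, with critical value 2.394.

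- Power at 0.82: Φ(2.821 − 2.394) = Φ(0.427) = 0.665. The t-based fall is from 0.797 to 0.648, or 80% to 65%.
- Restoring 80% needs 40 evaluable per group. With the protocol's own inflation: 40/0.85 → 48, then 48/0.92 → 53 per group, or 159 recruited against 120.

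**4. Cost of a fixed sequence.** The first test is the one in step 1, at 0.05. Its power and the target of 120 do not change.

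**The case against.** - **The level is inferred.** Data analysis states no alpha; 0.05 is written only under Sample size. A separate analysis plan, not seen here, could set an order, and a fixed sequence would fit the published sample size. This stands as a limit: the point concerns what the article fixes, which is three equal primary outcomes and a calculation that covers one.
- **Hypothesis 1 can be read as a conjunction.** It joins its outcomes with *and*. If all had to succeed there would be no inflation. The article neither states nor excludes this reading. It would also not match the sizing: if the three memory outcomes were independent, each with 80% power, the chance that all succeed would be 0.80³ = 0.51.
- **The plan has some structure.** It separates a main, an additional and a third aim, numbers the hypotheses, and gives each its contrasts. A reader might pool all four contrasts on three outcomes and put the risk at 20–34%. That figure reproduces, but it mixes hypotheses 1 and 3, which Table 2 keeps apart. A figure of 46% (1 − 0.95¹²) is not valid, because the four contrasts on one outcome are not independent.
- **Hypothesis 3 has its correct test.** Comparison 2 is ticked. A reader might infer that hypothesis 3 could be declared on comparison 3 alone, but nothing in the article says so. What remains is that comparisons 3a and 3b are listed as tests of a hypothesis they cannot test.
- **Another primary is defensible.** The Background singles out remembered pain as an expected effect. However, the article sizes the trial on intrusive thoughts and gives no standard deviation for remembered pain.

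**Conclusion.** The concern holds for hypothesis 1. With three unranked primary outcomes on comparison 1, the chance of at least one false positive is about 8–14%, or 1.7 to 2.8 times 0.05. This assumes that each outcome is tested at 0.05 (the only level given), that any one success counts, and that the outcomes correlate between 0.9 and 0. It covers only the three primary outcomes; hypothesis 1 also mentions overall dental experience, which is not counted.

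The documents do not support a headline of several times 0.05 for the trial as a whole, since the 20–34% range needs hypotheses 1 and 3 treated as one family. The Table 2 point is minor: comparison 3 does not test hypothesis 3, but the comparison that does is also there. The sample size arithmetic is sound.

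**What to change.** 1. Name intrusive thoughts on comparison 1 as the single primary test at two-sided 0.05. This is the test the trial is sized on.
2. Then test remembered pain and vividness of memories on comparison 1 in a pre-stated order, each at 0.05 and only if the test before it is significant.
3. Label the hypothesis 2 moderation tests and the hypothesis 3 contrasts as secondary, reported as estimates with confidence intervals.
4. In Table 2, base hypothesis 3 on comparison 2 only and report 3a and 3b as supporting estimates.

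This changes wording only. The target stays at 120, and Trial status reports only two patients randomized at submission.

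The cost is in what can be claimed. Confirmatory claims for remembered pain and vividness would depend on the intrusive-thoughts result, which has about a 20% chance of missing a true difference of 0.82. Hypotheses 2 and 3 would become non-confirmatory.

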**Trial registration:**

Current Controlled Trials ISRCTN41442806

## Background

Results from the latest National Health Service (NHS) Adult Dental Health Survey showed that over a third of adults (36%) suffer from moderate dental anxiety and another 12 percent from extreme dental anxiety [1]. Managing dental anxiety is recognized as an important issue in dental practice [2], since many people avoid or delay dental care because they experience fear and anxiety [3], and the expectation of pain is seen as a major barrier to seeking dental care [4]. Patients with dental fear tend only go to the dentist when they experience pain, thereby increasing the chance that their visit to the dentist will involve pain and exacerbating their anxiety [5]. Dentists themselves suffer from heightened discomfort when treating anxious patients [6]. Alleviating dental anxiety may also reduce perceived pain and unpleasantness [7], which may facilitate the work of dentists [2]. Dental anxiety and anxiety-related avoidance of dental care thus create a significant problem for both patients and the dental profession.

Previous poor medical experiences have been associated with anxiety and pain [8] and this may negatively impact the likelihood of patients complying with the required frequency of dental appointments. Moreover, anxious patients are less likely to keep their appointments [9], take longer to treat when they do attend, and afterwards feel less satisfied with their treatment [10]. Armfield and colleagues [5] provided evidence for the existence of a vicious cycle of dental anxiety. They demonstrated that people with high dental fear are more likely to delay dental treatment, which leads to more extensive dental problems and symptomatic visiting patterns, which in turn feed back into the maintenance or exacerbation of existing dental fear. Moreover, dental anxiety is associated with the tendency to experience negative or threatening thoughts concerning treatment [11].

Heightened emotion and arousal during an event increases the likelihood of recollections of the event being triggered uncontrollably by situational cues [12], for example, a whiff of antiseptic that triggers thoughts about dental treatment. Attempts at suppressing these intrusive thoughts tend to be counterproductive [13]. Once triggered, intrusive thoughts tend to be elaborated [14]. For example, an intrusive thought about going to the dentist might lead to the patient imagining how uncomfortable the next visit is going to be. According to the elaborated intrusion theory [14], the imagined experience not only simulates the sights and sounds of the experience but incorporates the actual emotions associated with that experience. This project aims to break this cycle of dental anxiety by providing pleasant imagery during dental treatment that distracts patients from treatment. We hypothesize that this imagery will block the development of intrusive memories of the dental experience, and render voluntary memories of the experience less vivid and less emotive; in particular, we expect remembered pain to be less intense.

There is a growing body of research that provides evidence that providing positive distractors in healthcare environments can impact health-related outcomes, such as anxiety and well-being of patients (for reviews, see [15,16]). Another review concluded that viewing nature scenes might decrease pain perceptions by eliciting positive emotional responses and decreasing stress levels [17]. Research on restorative environments suggests that certain environments, especially natural settings [18], are better at promoting recovery from stress. Lohr and Pearson-Mims [19] studied whether the presence of indoor plants would increase pain tolerance. Participants were placed in either a room with plants, a room with non-plant objects (as visually distracting as the plants), or a control room (no objects). A larger proportion of respondents in the room with plants were able to keep their hand in iced water for 5 minutes as compared with the participants experiencing the other conditions, suggesting increased pain tolerance by exposure to indoor plants. Both studies introducing real nature and studies using artificial nature interventions (for example, posters) show positive effects on patient outcomes [20-22]. Using nature to provide distraction in the dental clinic might thus lead to beneficial effects on the patient experience.

A variety of distraction interventions are used in daily medical practice to help patients cope with unpleasant procedures; these include watching television and listening to music [23,24]. We selected virtual reality (VR) as a vehicle for presenting nature to patients during dental treatment, based on evidence from a case study in dentistry showing that exposure to VR distraction is more effective in offering pain control than exposure to a video or a standard care situation without distraction [25].

Virtual reality goggles not only display potentially attractive visual stimuli to look at, they also exclude all other visual stimuli in the environment that might affect the patient. It has been suggested that, in medical surgical settings, the appearance of a nurse who cleans patient’s wounds can be strong enough to create anxiety [26]. The overhead light, the dentist with a facemask and the dental instruments might induce anxiety in a similar way. Virtual reality goggles effectively exclude the treatment environment and are thus a potentially interesting way of offering distraction to patients. Another reason why VR can be more effective than other distraction interventions is the difficulties some people may have in evoking images that are vivid enough to be effective distractors [27]. Additionally, using VR can offer a feeling of control. Previous research for example demonstrated that interactive VR, which offered more control possibilities, was better than passive exposure in children [28,29].

Several small-scale studies explored the use of VR in a dental context. A first study investigated the effects of using an audiovisual eyeglass system that displayed an instructional video [30]. Adult patients scheduled for dental prophylaxis were distracted during half of their treatment. At the end of the treatment, they were asked to compare the situation with and without the VR exposure. Patients reported less anxiety and discomfort when using the equipment. In another study, patients undergoing periodontal scaling and root planing procedures were exposed to a control situation (only wearing the headgear), a video (that is, the animation movie *Cars*) and a VR environment (of a botanical garden in *Second Life*) [31]. Both distracters, relative to the control condition, resulted in less pain and discomfort and lower blood pressure and pulse rate. Moreover, the VR environment scored significantly better on all indicators than the movie.

A range of VR environments has been studied, but a systematic approach to researching what type of environment might be more beneficial has not been taken before. Previous VR research looked at forests [27], a botanical garden [31] and snowy canyons [32,33] as well as a variety of video games [28,29,34]. Although natural and game-based distracters showed benefits, little is known about what sort of VR content is most effective at reducing stress and creating positive experiences and memories of treatment. Based on the evidence [18-22] that natural settings are more restorative than built environments, this research will compare a natural and an urban virtual environment, to test not only whether VR distraction is effective, but also to explore whether the content of the VR can make a difference.

### Aims and hypotheses

The main aim of the project is to determine whether the use of virtual nature during dental treatment can improve recollections of treatment and the overall dental experience. Additionally, we will look at the moderating role of patients’ baseline level of dental anxiety in these effects. A third aim is to test whether the content of the VR distraction can make a difference for its effectiveness by comparing two types of virtual environment, a natural environment and an urban environment.

#### *Objectives*

1. Determine the effectiveness of VR in improving recollections of treatment and the overall dental experience.

2. Determine the role of patients’ level of dental anxiety and test whether the use of VR could be especially beneficial for patients suffering from dental anxiety.

3. Determine any effect relating to the content of the VR.

#### *Overall hypotheses:*

1. Virtual reality exposure will lead to less intrusive thoughts, less vivid memories, less remembered pain and better overall dental experiences.

2. Dental anxiety will moderate the proposed effects under hypothesis 1. Patients with more dental anxiety will benefit more from the use of VR than patients with less dental anxiety.

3. The natural VR environment will be more effective than the urban VR environment.

#### *Additional predictions*

##### 

**Treatment experience** Compared with standard care, VR exposure (in general) will lead to less self-reported: (1) pain, (2) discomfort and (3) stress. It will also lead to (4) a lower average heart rate (an index of physiological stress) and (5) an underestimation of time elapsed (reflecting the ability of the VR environment to engage patients). For all of these outcomes, we further predicted that the natural VR environment will produce more positive outcomes than the urban VR environment. Additionally, we predict that (6) the use of VR will lead to more perceived control.

##### 

**Dental experience** Patients exposed to VR environments will show (7) lower subsequent levels of dental anxiety than those exposed to standard care and (8) improved intentions to revisit the surgery. Again we hypothesized that these effects would be greater in the natural than in the urban VR.

##### 

**Virtual reality experience** The natural VR environment will be perceived as more (9) attractive and (10) psychologically restorative than the urban environment. Moreover, (11) VR exposure will lead to a reduced awareness of the surrounding environment.

